## Abstract

**Background:**

Automated peripheral mechanical stimulation (AMPS) has been proposed as a new complementary therapy with potential for improving motor and cardiovascular abnormalities in Parkinson’s disease (PD). However, AMPS long-term effects and its combination with physical exercise are unknown. Thus, this study aims to compare the effects of a program of 12 weeks of physical exercise with a 12-week intervention program combining physical exercise and AMPS on the aerobic capacity, cardiac autonomic control, and gait parameters in patients with PD.

**Methods:**

A randomized, controlled clinical trial will be conducted. Older volunteers with PD will be randomly assigned to one of the two groups studied: (1) exercise or (2) AMPS + exercise. Both groups will undergo an exercise program of 24 sessions, for 12 weeks, performed twice a week. Before exercise sessions, the group AMPS + exercise will receive a session of active AMPS, while the group exercise will receive an AMPS sham intervention. Shapiro-Wilk’s and Levene’s tests will be used to check for data normality and homogeneity, respectively. In case parametric assumptions are fulfilled, per-protocol and intention-to-treat analyses will be performed using a mixed model analysis of variance to check for group*time interaction. Significance level will be set at 5%.

**Discussion:**

Several non-pharmacological treatment modalities have been proposed for PD, focusing primarily on the reduction of motor and musculoskeletal disorders. Regular exercise and motor training have been shown to be effective in improving quality of life. However, treatment options in general remain limited given the high prevalence and adverse impact of these disorders. So, developing new strategies that can potentiate the improvement of motor disabilities and also improve non-motor symptoms in PD is relevant. It is expected that the participants from both groups will improve their quality of life, gait parameters, and their cardiac autonomic control, with greater improvements being observed in the group combining active AMPS and physical exercise.

**Trial registration:**

ClinicalTrials.gov NCT04251728. Registered on February 05, 2020.

**Supplementary Information:**

The online version contains supplementary material available at 10.1186/s13063-021-05177-w.

## Administrative information

Note: the numbers in curly brackets in this protocol refer to SPIRIT checklist item numbers (Additional file 1). The order of the items has been modified to group similar items (see http://www.equator-network.org/reporting-guidelines/spirit-2013-statement-defining-standard-protocol-items-for-clinical-trials/).

## Introduction

### Background and rationale {6a}

Parkinson’s disease (PD) is a degenerative neurological disorder characterized by a loss of dopaminergic neurons at the substantia nigra level, leading to muscle tremor, rigidity, progressive bradykinesia, and postural instability, with great impact on the quality of life [1]. Based on international data, it can be estimated that there are more than seven million patients with PD worldwide [2]. Moreover, about 1 to 2% of the population over 65 years of age suffers from PD, rising to 3 to 5% in those over 85 years of age [3].

Gait disorders are one of the main therapeutic challenges in PD [4], involving a risk of fall, disability, and physical decline [5]. The progressive deterioration of the physical condition leads to a reduction in aerobic functional capacity and autonomy, thus affecting the ability to perform everyday tasks effectively [6, 7]. Indeed, it is estimated that between 40 and 70% of people with PD have falls, in which muscle weakness at lower limbs appears to play a key role, significantly reducing their postural stability [8]. These data allow us to consider elderly people with PD in a high degree of frailty, thus with high probability of suffering health problems due to the massive deterioration of physiological systems [9, 10].

In terms of intrinsic exercise capacity, studies have shown that the maximum oxygen uptake (VO_2_) of PD patients was no different from that of controls, but they reached their maximum VO_2_ earlier, suggesting a lower mechanical efficiency of movement during exercise, perhaps due to their muscle stiffness [11]. Moreover, some authors have studied the relationship between aerobic functional capacity and gait [12, 13]. Results showed a positive correlation between VO_2peak_ and gait speed, meaning that the lower the cardiorespiratory capacity the lower the gait speed.

Besides motor abnormalities, patients with PD present non-motor symptoms such as dysautonomia [14] and sleep disturbances [15]. Thus, physical exercise has been highly recommended as non-pharmacological intervention since it has shown to attenuate motor dysfunction, improve cognitive function, effectiveness of medications, and sleep patterns, as well as prevent depression and cardiovascular complications [16]. In this sense, Amara et al. mention that regular practice of physical exercise has positive effects on the effectiveness of sleep in the long term for patients with PD [17]. Furthermore, according to Fan et al. [18], physical exercise, especially those performed at moderate to vigorous intensities, has a positive impact on PD through multiple mechanisms, including reduction of α-synuclein protein accumulation, decrease in inflammation and oxidative stress, improvement in brain-derived neurotrophic factor (BDNF) activity, nerve regeneration, and mitochondrial function. Furthermore, some authors have shown that endurance exercise is safe and well-tolerated for people with PD from a cardiovascular point of view, which supports their recommendation for this population [19].

Although physical exercise has shown to be effective, some authors have proposed other non-pharmacological strategies as complementary therapy. In this sense, Barbic et al. [20] proposed an innovative approach aiming at improving walking parameters in PD. The authors evaluated the effect of a single session of peripheral mechanical stimulation therapy. After the stimulus, the authors observed significant changes in motor parameters such as improvement in gait length and gait speed. Concomitant to the motor improvement, surprisingly, there was an improvement in some cardiovascular parameters, such as decreased resting blood pressure and improved cardiovascular autonomic control in response to orthostatic stimulation. In addition, Zamunér et al. [21] studied the effects of five sessions of automated mechanical peripheral stimulation (AMPS) on cardiovascular parameters in patients with PD. The authors reported that after the AMPS therapy, patients with PD presented a decrease in cardiovascular sympathetic control and an improvement in arterial baroreflex sensitivity.

AMPS therapy consists of applying a mechanical pressure with intensity to elicit pain (at pain pressure threshold) at four specific points on the sole of both feet of patients with PD. Moreover, the total therapy duration is 96 s, and some studies have reported that the effects may last up to 72 h [22, 23]. Therefore, due to its promising beneficial results and that it is not a time-consuming therapy, AMPS represents an interesting intervention strategy. So, considering that AMPS therapy promotes beneficial motor and cardiovascular effects for PD patients in the short term, as well as physical exercise, it is important to study whether adding AMPS to an exercise rehabilitation program could potentiate the effects of exercise, since patients are expected to attend the sessions with the potential for improved performance and execution of the exercises during the sessions. Furthermore, no studies have addressed the long-term effects of AMPS (i.e., AMPS intervention program lasting more than 1 month) in patients with PD.

### Objectives {7}

The objectives of this study will be to evaluate the effect of 24 sessions of AMPS combined to a physical exercise program performed twice a week for 12 weeks on aerobic functional capacity, gait parameters, and cardiac autonomic control in patients with PD. As a hypothesis, the exercise program combined with AMPS therapy is expected to be more effective in improving cardiac autonomic control and aerobic functional capacity in PD patients than exercise alone.

### Trial design {8}

The present study is a two-arm parallel double-blind randomized controlled trial. The sample will be selected on a non-probability basis. Participants will be randomly assigned in a 1:1 ratio to one of the two groups: (1) exercise group (EX-G) or (2) group combining AMPS and exercise (AMPS-G).

## Methods: participants, interventions, and outcomes

### Study setting {9}

The study will be carried out at the Laboratory of Clinical Research in Kinesiology from the Universidad Católica del Maule, Talca, Maule, Chile and Human Movement Research Laboratory (MOVI-LAB), Bauru, Brazil.

### Eligibility criteria {10}

#### Inclusion criteria

Volunteers must present a clinical diagnosis of PD, made by a board-certified neurologist, according to the UK Brain Bank criteria [24] aged 50 years or over and be classified as 1 to 3 at the Hoehn and Yahr scale. Drug treatment of volunteers should remain unchanged for at least 30 days prior their inclusion in the study.

#### Exclusion criteria

Volunteers who show signs of cognitive impairment, based on the results of the Mini-Mental State Examination adjusted for the educational level of the Chilean and Brazilian population [25], who present cardiorespiratory, neuromuscular, and musculoskeletal diseases will be excluded. Volunteers who have peripheral sensory neuropathy, diabetes, or any other condition or disease known to promote autonomic dysfunction will be excluded based on symptoms, physical condition, and routine laboratory tests.

### Who will take informed consent? {26a}

[name] researcher will be in charge to contact potential participants via telephone and invite them to participate in the study. In case we have a positive reply, an appointment will be scheduled and [name] will explain the objectives of the study, the inclusion and exclusion criteria, participant’s roles, risks, benefits, and ethical implications. If the participants agree in took part in the study, they will be requested to sign two copies of an informed consent, one for the participants and the other for the researcher.

### Additional consent provisions for collection and use of participant data and biological specimens {26b}

Not applicable, this trial does not have biological specimens.

### Interventions

#### Explanation for the choice of comparators {6b}

In order to comply with the proposed objective and verify whether AMPS therapy improves exercise performance by enhancing its benefits and taking into account a possible placebo effect, participants will be randomly assigned to one of the two studied groups: (1) exercise group (EX-G): participants will undergo 12-week exercise program, held twice a week along with 2 weekly sessions of inactive SHAM during the same period; (2) group combining AMPS and Exercise (AMPS-G): participants in this group will undergo the same 12-week exercise program of the EX-G, along with 2 weekly sessions of active AMPS during the same period.

#### Intervention description {11a}

##### Automated mechanical peripheral stimulation

AMPS therapy will be applied through a therapeutic device (Gondola, Ecker Technologies, Lugano, Switzerland), which will be fitted to each patient’s feet. The device consists of a foot stand for each foot with two electric motors that activate two 2-mm-diameter metal bars. The mechanical pressure stimulus occurs when the motors are activated. Before application, the device is adjusted so that the stimulus is applied to two specific areas for each foot, at the base of the first metatarsal joint and at the head of the hallux of the right and left feet. The intensity of the pressure is adjusted to reach the participant’s pain threshold (which normally occurs around 0. 3–0. 9 N mm^2^), defined as the moment when the participant reports that they began to feel pain (the moment of transition between the strong pressure and the painful pressure and the first time the visual analog scale (VAS) is greater than 0) or at the moment when the monosynaptic reflex appears in the anterior tibial muscle. After these preparatory procedures, treatment begins. The therapy will be carried out in 4 cycles. A cycle is completed when the four target areas are stimulated, which requires 24 s (6 s per area) so the complete therapy lasts 96 s [26].

The SHAM intervention will replicate the same procedure described for active AMPS. However, a rubber adapter will be positioned at the tip of the metal bars to increase the contact surface area and the pressure will be set to the sensorial threshold (i.e. when the patient report that they feel a touch at the point). AMPS sessions will be performed 24 h before all the exercise sessions [27].

##### Physical exercise program

Physical exercise sessions will be composed of:
Warm-up (5 min): patients perform stretching of the main muscle groups of the upper limbs, lower limbs, and trunk.Aerobic exercise (30 min): Patients will perform continuous aerobic exercise consisting of walking on flat ground and ramps, with intensity between 40 and 60% of the heart rate reserve.Strengthening exercises (20 min): volunteers will perform resistance exercises (2 series × 15 repetitions) for the upper and lower limbs, and the trunk working the following muscle groups: shoulder flexors, extensors, and abductors; elbow flexors and extenders; trunk extensors and flexors; knee flexors and extenders; and dorsiflexes and plantar flexors.Cool down (5 min): Stretching of the main muscle groups worked during the sessions and relaxation.

After 6 weeks and in the end of the intervention program, the participants will be asked to inform which kind of intervention they thought they had been on (i.e., placebo or active) and to report their confidence level rating on a scale of 0–10, with 0 meaning “not at all confident” and 10 “extremely confident” that they received the active therapy [28].

#### Criteria for discontinuing or modifying allocated interventions {11b}

Participants who attend less than 70% of the training sessions, participants who have been absent on evaluation days and participants who start performing other regular physical exercises after baseline assessments will be excluded from the study.

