#### Relevant concomitant care permitted or prohibited during the trial {11d}

Participants will be allowed to keep their pharmacological treatment during the entire study. However, participants will be excluded in case of any dose modification during the trial. In addition, participants may continue to attend physiotherapy interventions and any other non-pharmacological interventions if it is a regular practice started at least 6 months before the study. In this case, participants will be requested to maintain this activity during the entire study; otherwise, they will be excluded.

However, they will be excluded in case of suspension of any intervention or start of a new regular intervention. For the outcome assessments performed at baseline and after the intervention program, participants will be instructed not to drink alcohol and/or stimulants (coffee, teas, and energy drinks), avoiding heavy meals, having a light meal at least 2 h before the test and not doing strenuous exercise 48 h before the evaluations.

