#### Procedure for unblinding if needed {17b}

In case a participant report to know their intervention group during the trial, it will be immediately communicated to the leading researcher and the participant will be excluded from the study. At the end of the study, in case the treatment is effective, it will be offered to these participants.

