#### Methods in analysis to handle protocol non-adherence and any statistical methods to handle missing data {20c}

Per-protocol and intention-to-treat analysis will be performed. Per-protocol analysis will include only participants who attended at least 70% of the sessions and underwent baseline and final evaluations. Missing data will be addressed by a multiple imputation method.

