#### Adverse event reporting and harms {22}

In the end of each intervention session, participants will be asked to report any complaints and symptoms produced by the proposed activity. Outcome assessor and the lead researcher will be in charge to collect and record this information throughout the study. Adverse events, undesirable effects, and incidents will be classified by specialists as treatment-related or non-treatment-related within 24 h of occurrence [41]. Common undesirable effects may include fatigue, dyspnea, and muscle soreness not lasting more than 24–48 h as a result of the exercise and AMPS intervention. In case these symptoms persist, or other related-treatment event occur, the participants will be asked to discontinue from this study and this will be immediately informed to the ethics committee who will decide whether the protocol should be suspended. All complications and dropouts will be reported in the final manuscript.

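### Rules that exclude randomised participants from the study conflict with the promised intention-to-treat analysis and open the comparison to selection bias

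*Protocol article*

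**What the plan says.** Four sections of the protocol article take participants out.

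- **Criteria for discontinuing or modifying allocated interventions {11b}** names "Participants who attend less than 70% of the training sessions, participants who have been absent on evaluation days". It goes on: "participants who start performing other regular physical exercises after baseline assessments will be excluded from the study".
- **Relevant concomitant care {11d}**: "participants will be excluded in case of any dose modification during the trial". For other therapies, "they will be excluded in case of suspension of any intervention or start of a new regular intervention".
- **Procedure for unblinding {17b}**, for a participant who reports knowing the allocation: "it will be immediately communicated to the leading researcher and the participant will be excluded from the study".
- **Adverse event reporting and harms {22}**, for symptoms that persist or other treatment-related events: "the participants will be asked to discontinue from this study".

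The section on non-adherence and missing data {20c} then says: "Per-protocol and intention-to-treat analysis will be performed". It limits the per-protocol set to participants with at least 70% attendance and both evaluations, and adds: "Missing data will be addressed by a multiple imputation method".

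Implementation {16c} has the envelope opened after the baseline assessments and before the intervention starts. Outcomes {12} sets two assessment times, baseline and after 12 weeks.

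**The concern.** An ITT analysis keeps every randomised participant in the assigned group, whatever happens afterwards. Here the conditions for remaining in the study are nearly the conditions for entering the per-protocol set. No section says that a participant removed under these rules is still assessed at week 12 or kept in the ITT set.

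The reasons for removal may also be linked to treatment or prognosis. The intervention description {11a} sets active stimulation at the pain threshold and sham at the touch threshold. Discomfort, and the ability to recognise one's allocation, could therefore differ by arm. A dose change may follow a change in symptoms. If removals differ between arms and relate to outcome, the groups compared are no longer the randomised groups. With 25 enrolled per arm, a few such removals matter.

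**Working it through.** **1. Rules side by side**

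| Ground for removal | Section | Consequence stated | Also in the {20c} per-protocol definition? |
|---|---|---|---|
| Under 70% of training sessions (0.70 × 24 = 16.8, so fewer than 17) | {11b} | excluded from the study | yes |
| Absent on an evaluation day | {11b} | excluded from the study | yes |
| New regular exercise | {11b} | excluded from the study | no |
| Dose modification | {11d} | excluded | no |
| Therapy stopped or started | {11d} | excluded | no |
| Reports knowing the allocation | {17b} | excluded from the study | no |
| Persisting symptoms or treatment-related event | {22} | asked to leave the study | no |

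Both per-protocol criteria are already conditions for staying in the study. Read literally, everyone left in the study meets them, so the two analysis sets nearly coincide.

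**2. Timing**

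By {16c}, low attendance, a missed final evaluation, changes during the trial, reported knowledge of the allocation and adverse events all fall after randomisation. Absence from the baseline evaluation falls before it. New exercise taken up after baseline could fall on either side of the envelope opening.

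**3. The plan's own figures**

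Sample size {14} gives 19 per group for an effect size of 0.80 and enrols 25. No dropout rate is stated. The implied allowance is 1 − 19/25 = 0.24, or 6 per group, and 19/(1 − 0.24) = 25 confirms it. The normal-approximation formula 2(z₁ + z₂)²/0.80², at 80% power, rounds up to 20 per group one-sided and 25 two-sided, so 19 is close only to the one-sided result. That is a separate matter. Here 24% and 0.80 serve only as yardsticks.

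**4. Worst case**

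Assumptions not in the documents: normal outcome, no true effect, and exactly the worst fraction q of one arm removed with none from the other. The mean of the remaining arm shifts by φ(z_q)/(1 − q) SD.

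| q | φ(z_q)/(1 − q) | Share of 0.80 |
|---|---|---|
| 0.10 | 0.1755/0.90 = 0.195 | 0.24 |
| 0.20 | 0.2800/0.80 = 0.350 | 0.44 |
| 0.24 | 0.3109/0.76 = 0.409 | 0.51 |

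**5. Milder case**

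Again assumed: no true effect, 25 per arm, and removal driven by a latent variable with correlation 0.3 to 0.5 to the outcome. There were 4,000 simulated trials per scenario, each analysed with a two-sided 5% t-test.

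| Removed, arm 1 v arm 2 | Bias (SD) | Type I error |
|---|---|---|
| 24% v 24% | about 0 | 5.2% to 5.9% |
| 24% v 12% | 0.06 to 0.10 | 5.2% to 6.7% |
| 24% v 0% | 0.12 to 0.20 | 7.1% to 10.4% |
| 40% v 8% | 0.14 to 0.24 | 7.0% to 11.7% |

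As a check on the third row, the worst-case shift times the correlation gives 0.409 × 0.3 = 0.12 and 0.409 × 0.5 = 0.20.

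**The case against.** The best defence is that *excluded* is used loosely. The {11b} heading concerns stopping or modifying interventions. A per-protocol set confined to good attenders with both evaluations is only worth defining if the ITT set also holds people who fail those tests. On that reading ITT is feasible. This is plausible, but two sections say removal is from the study, and none says that follow-up continues. The conflict therefore stands as a matter of text.

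Several stronger readings are tempting and are not supported:

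- **That ITT cannot be carried out at all.** It is undermined as written. Clarified wording would restore it.
- **That imputation would have nothing to act on.** Retained participants can lack single measurements, such as an unusable heart-rate recording or an incomplete exercise test. A low attender or someone with a dose change may still have a week-12 value, and removed participants have baseline data.
- **That every ground for removal follows randomisation.** Most do; step 2 shows the exceptions.
- **That exclusions could create or hide an effect of the planned size.** Even removing the worst 24% of one arm gives 0.41 SD, about half of 0.80.
- **That training attendance will differ by arm.** The exercise programme is the same in both arms and stimulation is given 24 hours earlier. Recognition of the allocation is the more direct route to a difference, and that too is a possibility, not a finding.

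Which analysis is primary is commonly left to a statistical analysis plan, which is not shown, so it is not raised here.

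**Conclusion.** The point holds as a conflict between sections {11b}, {11d}, {17b} and {22} on one side and {20c} on the other. Applied literally, the rules reduce the ITT set to roughly the per-protocol set, provide for no week-12 data on those removed, and leave the comparison open to selection bias.

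The documents fix neither the size nor the direction of that bias, since both depend on whether removals differ by arm and relate to outcome. Under the assumptions above it is about 0 with equal removals unrelated to arm, and about 0.1 to 0.2 SD with 24% removed from one arm only. The figure of 0.41 SD is the ceiling when 24% is removed from one arm only. It is not an expected value, and it does not bound larger losses or selective losses in both arms.

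**What to change.** - In {11b}, {11d} and {17b}, separate stopping the intervention, or leaving the per-protocol set, from leaving the study.
- Seek the week-12 assessment from every randomised participant who consents and for whom it is clinically appropriate.
- In {20c}, state that the ITT analysis includes all randomised participants in their assigned group, with imputation for missing week-12 values.
- Use the listed events only to define the per-protocol set, and extend the {20c} definition to name all of those intended.
- Reconcile {22} with {20c}, so that it is clear whether a participant who stops because of an event remains in follow-up and in the ITT set. The clinical decision stays with the sponsor.

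The cost is protocol wording, some additional week-12 visits and a somewhat diluted effect estimate. Whether anyone continues to receive the intervention need not change.
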